### Stool test

A Stool test will be done for work package two to identify factors associated with undernutrition.

Stool samples will be collected in clean, leak-proof stool cups using conventional methods. It will be tested shortly after collection using direct procedures. Direct microscopy to identify motile protozoa and the Kato-Katz stool test for the presence and severity of infection will be assessed for Ancyclostoma duodenale (hookworm), Ascaris lumbricoides (roundworm), and Trichuris trichiura (whipworm) ova.

### Blood collection and lab analysis

A 5–6 ml of venous blood will be collected via venepuncture, and then four millilitres will be transferred to a serum separator tube (SST) for biochemical analysis, and the remaining two will be drawn into to tube containing ethylene diamine tetraacetic acid (EDTA) for complete blood count (CBC) analysis. During blood collection, all infection prevention standards will be applied. The blood samples in the EDTA tubes will be wrapped in aluminium foil, continuously shielded from light during transportation to Hawassa Referral Hospital for CBC analysis.

The collected blood in SST will be allowed to clot for 30 minutes and centrifuged at 4000rpm for 10 minutes. After centrifuging, serum will be kept in a cryo vial tube with the participant’s identity and will be transported to Hawassa Referral Hospital using a cold chain carrier at −20°C. Biochemical analysis will be held at Hawassa Referral Hospital laboratory department using Cobas 6000 immediately (if possible) or stored at −70°C until analysis.

Haemoglobin will be determined using a complete blood count (CBC) machine (Sysmex Kx-21 automated analyser, Sysmex Corporation, Kobe, Japan) with a venous blood sample. Serum ferritin, iron, Vitamin B12, and folate will be analysed by electrochemiluminescence immunoassay (ECLIA) on Cobas 6000 (e601 module). The measuring principle for CRP and α 1-Acid glycoprotein (AGP) will be analysed using a particle-enhanced immunoturbidimetric assay and measured on Cobas 6000 (c501 module). Results will be determined via a calibration curve, which is an instrument specifically generated by 2-point calibration and a master curve provided via the reagent barcode.

To evaluate the impact of the Amaranth plus flaxseed food products on Education outcomes, measurements like enrollment, attendance, and test scores will be considered as outcome variables. School enrollment measures the student’s admission to a specific class and will be checked from the school’s list of students and their assignment to a specific class. The school attendance variable measures the rate of students’ absenteeism from school. The variable will be collected from the attendance sheet that will be registered every day before the day’s class starts. The test scores variable will be measured using the standard test exam results. Students will write Language, Mathematics, and General Sciences exam papers three times (Baseline, Mid-term, and end of intervention) during the intervention period.

The same exam papers will be used throughout the study. Progress will be monitored before, during, and after the intervention. Education professionals will prepare the exams, with a committee of four members per subject (12 total) trained to develop standard questions. A strict invigilation process will be enforced, with 10 trained invigilators from each school overseeing the simultaneous administration of exams for both control and treatment groups. Additional child and caregiver data will be sourced from the main project’s baseline and end-line surveys.

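### Serum may be assayed at once or after −70°C storage with nothing tying the two trial schools together, so a handling difference in one school at one visit would be inseparable from the food effect

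*Protocol article*

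**What the plan says.** The section on blood collection and lab analysis divides each venous sample in two. The EDTA portion goes for a blood count: "Haemoglobin will be determined using a complete blood count (CBC) machine". Light protection is mentioned for this portion only: "The blood samples in the EDTA tubes will be wrapped in aluminium foil, continuously shielded from light during transportation". The other portion goes into a serum separator tube, clots for 30 minutes, and is spun at 4000 rpm for 10 minutes. "After centrifuging, serum will be kept in a cryo vial tube", and it "will be transported to Hawassa Referral Hospital using a cold chain carrier at −20°C".

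The two paths then open: "Biochemical analysis will be held at Hawassa Referral Hospital laboratory department using Cobas 6000 immediately (if possible) or stored" at −70°C. The assays are also named: "Serum ferritin, iron, Vitamin B12, and folate will be analysed by electrochemiluminescence immunoassay". The section does not name the HDL assay. I take it to belong to the biochemistry for which the serum tube is drawn.

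Three other parts of the article bear on the point:

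- The sampling procedure for WP 2 and 3 picks two of the six survey schools for the pilot and randomises one to each food. Children from the survey are invited into the trial.
- The section on outcome measures makes change in serum iron, ferritin, folate, vitamin B12 and HDL part of the WP3 outcomes.
- Table 2 lists the blood markers over May to September before feeding, and again in December.

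**The concern.** The text permits two handling paths and lets practical circumstances decide between them. In a trial with many clusters per arm, or with individual randomisation, that would mostly add noise. Here each arm is a single school. Whatever happens to one school's samples and not to the other's also happens to one arm and not to the other.

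The path could easily follow the school. If one school's endline serum arrives when the analyser is free and the other's arrives when it is not, one arm is assayed at once and the other after storage, probably in a different run and perhaps with a different reagent lot. Any resulting shift would be read as an effect of the amaranth and flaxseed bread, or would hide one. It could not be corrected once the samples had been used.

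**Working it through.** The document gives no assay bias or assay variability, so there is no stated figure to reproduce. The check is to see which handling differences survive in the comparison that the plan will make.

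**Inputs**

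- Two schools, A and B, one per arm (sampling procedure for WP 2 and 3).
- Two blood measurements, before feeding (visit 1) and at the end (visit 2) (Table 2).
- The outcome is a change (outcome measures).
- Handling is free to vary (blood collection and lab analysis).

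**Set-up.** Let h(A,1), h(A,2), h(B,1) and h(B,2) be the average shift that storage, run or reagent lot puts into each school's results at each visit. The difference in changes between the schools then estimates

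true food effect + [h(A,2) − h(A,1)] − [h(B,2) − h(B,1)].

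**Cases**

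| Handling pattern | Bias in the difference in changes |
|---|---|
| Same shift h in both schools at visit 2 only | h − h = 0 |
| Same shift h in school A at both visits | (h − h) − 0 = 0 |
| Shift h in school A at visit 2 only | h |
| Shift h in school A at visit 1 only | −h |
| Shift h in a fraction f of school A's samples at visit 2 only | f × h |

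The zeros are exact for an additive shift. For a proportional shift the cancellation is close but not complete, because a residue remains where the school or visit means differ. Only a school-by-visit pattern does real damage.

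**Can analysis remove it?** If each school at each visit contains a mixture of immediate and stored samples, and the path is recorded, an adjustment is conceivable. If a whole school takes one path at one visit and the other three groups take the other path, the handling indicator is identical to the school-by-visit term that carries the treatment effect. No model can then separate them.

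**Scale, for illustration only.** Suppose, with no support from the document, a shift of 5 to 10% of the mean and a between-child SD of 30 to 40% of the mean. Suppose also that a whole school is affected at one visit only. In units of that between-child SD:

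- smallest: 5/40 = 0.125 SD
- largest: 10/30 = 0.33 SD

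The WP3 sample size assumes an effect of 0.5, so these are 0.125/0.5 = 25% and 0.33/0.5 = 67% of it. This is the worst pattern with assumed inputs. It shows that the mechanism could matter, not that it will.

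**What is untouched.** Haemoglobin comes from the EDTA tube and has no immediate-or-stored choice. Anthropometry and education outcomes are not involved.

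**The case against.** Several points on the other side are fair.

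- The text states a preference for immediate analysis, with storage as a fallback, and all serum shares the same clotting, spinning and −20°C transport. This is so, and the two paths should not be called fresh and frozen. The fallback is still a second path with no rule attached.
- Nothing says that the schools will be bled on different days or assayed separately. That stands: a school-aligned difference is permitted, not planned.
- Much of the pre-feeding sampling in Table 2 precedes the September randomisation. That limits allocation-driven differences at baseline. It does nothing for the end measurement, or for logistical differences between schools.
- The article plans standardisation of micronutrient measures, calibration against a master curve, and data collectors unaware of allocation. These help against analyser drift and deliberate differences. They do not equalise storage or runs between schools.
- An article may leave laboratory detail to a full protocol. Here, though, the handling rule is stated, alongside clotting time, spin speed, transport temperature and analyser modules. The objection is to what the rule allows, not to an omission.

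A reader might also infer from the foil sentence that serum is left unshielded, that folate and vitamin B12 readings fall as a result, and that the WP2 survey will overstate deficiency. The document does not support this. It is silent on shielding of serum, which is not a statement that there is none, and it nowhere says that these analytes are affected by light. What remains is an asymmetry in the wording that the sponsor can clear up in a line.

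**Conclusion.** The point holds as a weakness in a stated rule. With one school per arm and changes in serum markers as outcomes, an open choice between "immediately (if possible) or stored at −70°C until analysis" leaves room for a school-by-visit handling difference that could not be told apart from the effect of the food. Shifts shared by both schools at a visit, or constant within a school, largely cancel and are not the worry.

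The size cannot be derived from the document, and the 0.125 to 0.33 SD range should not be quoted as an estimate. The conclusion rests on one school per arm, on comparison of changes between schools, and on HDL being measured in the same serum. It does not say that such a difference will occur. The change is worth making because it is cheap beforehand, while the damage could not be repaired afterwards.

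The protocol already takes this kind of care elsewhere: it has both groups sit their exams at the same time. The blood outcomes deserve the same protection.

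**What to change.** In the section on blood collection and lab analysis, replace the immediate-or-stored choice, for the two trial schools, with one rule:

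1. Collect blood from both schools over the same period at each visit.
2. Store all WP3 serum at −70°C.
3. At each visit, assay both schools' samples interleaved in the same runs and with the same reagent lot.
4. Label the samples with codes that do not show the school.

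Where the baseline serum comes from the WP2 survey, before the two trial schools have been chosen, apply the same single storage and run rule across all six survey schools. Otherwise the baseline of the two schools chosen later may already differ in handling.

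Also ask the sponsor to confirm whether the foil sentence was meant for the EDTA tube, the serum tube or both.

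The cost is that WP3 biochemistry results arrive later. No extra samples or assays are needed, and −70°C storage is already planned. The document does not describe freezer capacity, so the sponsor should check that it can hold all the samples.

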#### Eligibility

Inclusion Criteria: Accenting grade 1–2 actively, learning in school children (7–10 years old) with consenting parents or guardians at selected primary schools will be included.

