## Statistical data analysis:

The statistical software SPSS version 27 and STATA version 16 will be used for data analysis. To determine if the data are normally distributed, a one-sample Kolmogorov – Smirnov test will be used. Mean and standard deviation will be reported for normally distributed data, while median and interquartile ranges will be reported for non-normally distributed data. Parametric analysis will be used to analyse data that will be normally distributed, and nonparametric analysis will be used to analyse data that will not be normally distributed. One-way ANOVA will be used to determine the significance of the mean difference of scores for colour, appearance, flavour, taste, consistency, mouth feel, and overall acceptability (work package I), and also to compare the serum levels of trace elements among the participants (work package II and III). The mean score of proximate composition, mineral, and phytate will be analysed by using the mean difference to determine the significant change. Each determination of nutrient measurement will be carried out on three separate samples and will be analysed in triplicate (work package I). Using the WHO Anthro-Plus version 10.4 software, the z-score values for height, weight, and BMI for age will be determined (work packages II and III). To assess the effects of energy and nutrient-dense amaranth-based food on nutritional status and educational attainments, intention-to-treat (ITT) analysis will be used (work package III). Data will be presented as frequency, percentages, mean, standard deviation, and mean difference. A p-value of < 0.05 will be statistically significant in all analysis (work packages I-III).

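### Test scores from a pooled grade 1 and 2 sample are not tied to grade in their scale or comparison; standardise within grade and adjust for grade and baseline score.

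*Protocol article*

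**What the plan says.** All references are to the protocol article.

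- **Population.** Under Eligibility, the pilot takes "Accenting grade 1–2 actively, learning in school children (7–10 years old) with consenting parents or guardians". The two grades form one sample.
- **Outcome.** The PICO list gives test score, with dropout, as the education outcome. The education paragraphs at the end of the section on blood collection and laboratory analysis define it: "The test scores variable will be measured using the standard test exam results".
- **Instrument.** The same paragraphs say "Students will write Language, Mathematics, and General Sciences exam papers three times (Baseline, Mid-term, and end of intervention") and "The same exam papers will be used throughout the study". On who sets the papers: "Education professionals will prepare the exams, with a committee of four members per subject (12 total) trained to develop standard questions". Subject is specified; grade is not mentioned.
- **Analysis.** Under Statistical data analysis, for "nutritional status and educational attainments, intention-to-treat (ITT) analysis will be used (work package III"). The general reporting line is "Data will be presented as frequency, percentages, mean, standard deviation, and mean difference". No grade stratum, covariate or grade-referenced score is named. Height, weight and BMI, by contrast, are converted to age-referenced z-scores with named software.
- **Sampling.** Under Sampling procedure for WP 2 and 3, children are drawn in proportion to class size, and two of the six survey schools, chosen to be comparable, are then allocated at random, one to each arm.

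**The concern.** Grade 2 children have had a year more of schooling than grade 1 children, so a gap in exam performance between the grades is to be expected. The text does not say whether both grades sit the same paper. If they do, the gap becomes part of the spread of the pooled marks. If each grade has its own paper, the marks are on two scales, and a pooled mean or pooled raw gain has no clear meaning.

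The design adds a second route. With one school per arm, random allocation cannot balance the grade mix, and sampling in proportion to class size makes the mix follow each school's enrolment. A difference in mix would then appear as a difference in mean score between arms and could be read as an effect of the bread.

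**Working it through.** **The plan's own figure.** The work package 3 sample size uses a standardised effect of 0.5, 80% power and 1:1 allocation. A two-sample t test at two-sided alpha 0.05 needs 63.8 per group, so 64 per group and 128 in total, as stated. Then 128 × 2 (design effect) = 256, and 256 × 1.10 (attrition) = 281.6, rounded to the stated total of 282. The outcomes listed for this calculation are ferritin, folate, vitamin B12, haemoglobin, weight, height and HDL. Test scores are not among them, so no stated figure depends on the exam scale.

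**Assumptions.** The documents give no gap between grades and no grade mix. Let the within-grade SD be 1, let grade 2 score g above grade 1, and let p be the share of children in grade 2.

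**Spread.** Pooled SD = √(1 + p(1 − p)g²). With p = 0.5 this is √(1 + g²/4).

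**Shift.** If the grade 2 share differs by Δ between the two schools, the raw end-line difference in means moves by g × Δ.

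| Assumed gap g | Pooled SD | Rise in SD | Shift, Δ = 0.10 | Shift, Δ = 0.20 |
|---|---|---|---|---|
| 0.25 | √1.0156 = 1.008 | 0.8% | 0.025 | 0.05 |
| 0.5 | √1.0625 = 1.031 | 3.1% | 0.05 | 0.10 |
| 1.0 | √1.25 = 1.118 | 11.8% | 0.10 | 0.20 |
| 1.5 | √1.5625 = 1.250 | 25% | 0.15 | 0.30 |

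Shifts are in within-grade SD units. With Δ = 0 the shift is zero whatever the gap. The rise in SD needs no imbalance, only a gap between grades.

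**Using the baseline exam.** If both grades sit a common paper and change from baseline is analysed, a constant gap g cancels. What remains is h × Δ, where h is the difference in gain between grades. For assumed h of 0.1 to 0.3 and Δ of 0.10 to 0.20, this runs from 0.1 × 0.10 = 0.01 to 0.3 × 0.20 = 0.06 SD.

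**The case against.** The strongest objection is that the text nowhere says raw end-line marks will be compared. The mean difference appears in a general reporting line, not in a model for exam scores. A journal article may leave the scoring scale and covariates to the full protocol or analysis plan. A baseline exam exists, progress is to be followed across the three sittings, and the sample size section mentions ten unnamed predictors, which could include grade. The schools are to be comparable and the sampling is called stratified, though neither statement names grade. All of this stands: pooling of plain marks is an inference, and an unequal grade mix is not documented.

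A reader might go further and infer that the education comparison is underpowered. Holding the effect at 0.5 within-grade SD, power at 64 per group would fall from 80% to 78%, 71% or 61% for gaps of 0.5, 1.0 or 1.5. The documents do not support that reading. The 0.5 is a conventional value that is not tied to a within-grade SD, and the calculation was not made for test scores. A reader might also infer that the education result is already biased by grade. That would require both an unequal mix and an analysis that ignores the baseline exam, and neither is stated.

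What survives is narrower. An analyst who follows only what is written has exam results, intention-to-treat and a mean difference, and nothing there keeps grade out of the comparison.

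**Conclusion.** The point holds as an inexpensive improvement to the analysis, not as an error in a stated number. Two grades are pooled, and neither the exam score nor the comparison is tied to grade. If marks are pooled, the spread widens whenever the grades differ in mean, and the end-line comparison shifts whenever the two schools differ in grade mix.

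The size cannot be derived from the documents. For assumed gaps of 0.5 to 1.5 within-grade SD, the pooled SD rises 3% to 25% with an equal split, and a 10-point mix difference moves a raw end-line comparison by 0.05 to 0.15 SD. The shift is zero with equal mix, and on a common paper most of it goes if change from baseline is used. The sample size and power statements are unaffected.

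**What to change.** - State whether each grade sits its own paper.
- Standardise each subject score to the baseline mean and SD of the child's own grade, with both schools combined: z = (score − baseline mean for that grade and subject) / baseline SD for that grade and subject. Apply the same baseline mean and SD at every sitting.
- Compare arms on the standardised score with grade and baseline score in the model. The grade term also absorbs a difference in gain between grades, which standardising to baseline alone would leave.

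The cost is a sentence or two of analysis wording. Enrolment is by grade and the baseline exam is already planned, so no data collection is added. The change does not remove the confounding of school with arm: with one school per arm, any other difference between the two schools still enters the comparison, and the report should say so.

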## Outcome measures variables

The study will report on: WP1: nutrient content; sensory attribute of formulated food; WP2: prevalence and causes of nutritional anaemia (serum iron, haemoglobin, serum ferritin, vitB12, folic acid); level of high-density lipoprotein (HDL) to look at the effect of healthy fat intake from flaxseed mix; and WP3: change in nutritional anaemia (serum iron, ferritin, folate and Vit B-12), change in HAZ, BMI/age, WAZ and HDL, and acceptability of amaranth plus flaxseed food are the outcome variables of this study.

## Statistical data analysis:

The statistical software SPSS version 27 and STATA version 16 will be used for data analysis. To determine if the data are normally distributed, a one-sample Kolmogorov – Smirnov test will be used. Mean and standard deviation will be reported for normally distributed data, while median and interquartile ranges will be reported for non-normally distributed data. Parametric analysis will be used to analyse data that will be normally distributed, and nonparametric analysis will be used to analyse data that will not be normally distributed. One-way ANOVA will be used to determine the significance of the mean difference of scores for colour, appearance, flavour, taste, consistency, mouth feel, and overall acceptability (work package I), and also to compare the serum levels of trace elements among the participants (work package II and III). The mean score of proximate composition, mineral, and phytate will be analysed by using the mean difference to determine the significant change. Each determination of nutrient measurement will be carried out on three separate samples and will be analysed in triplicate (work package I). Using the WHO Anthro-Plus version 10.4 software, the z-score values for height, weight, and BMI for age will be determined (work packages II and III). To assess the effects of energy and nutrient-dense amaranth-based food on nutritional status and educational attainments, intention-to-treat (ITT) analysis will be used (work package III). Data will be presented as frequency, percentages, mean, standard deviation, and mean difference. A p-value of < 0.05 will be statistically significant in all analysis (work packages I-III).

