### Flour blend formulation

The flour blends from prepared flours will be formulated for the preparation of a recipe for standardised food preparation. The grain ratio will assess the combination that has the highest nutritive value (nutrients and energy), the lowest anti-nutrient ratio to nutrient and acceptable taste, texture and preparation qualities.

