### Acceptability

A consumer acceptability test will be done at the laboratory and community levels by using nine-point hedonic tests. Community acceptability tests will be done with school children.

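### One-way ANOVA of the work package 1 hedonic scores ignores pairing, and so loses power, if tasters score more than one blend; the article does not say whether they do

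*Protocol article*

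**What the plan says.** Under Flour blend formulation, several blends are to be compared: "The grain ratio will assess the combination that has the highest nutritive value (nutrients and energy), the lowest anti-nutrient ratio to nutrient and acceptable taste". Taste is thus one selection criterion beside nutritive value and anti-nutrient content.

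Under Acceptability: "A consumer acceptability test will be done at the laboratory and community levels by using nine-point hedonic tests". The community part uses children: "Community acceptability tests will be done with school children".

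The section Statistical data analysis names the test for work package 1: "One-way ANOVA will be used to determine the significance of the mean difference of scores for colour, appearance, flavour, taste". Three further attributes follow in that sentence, seven in all. It names no taster, block or repeated-measures term. The significance level is general: "A p-value of < 0.05 will be statistically significant in all analysis (work packages I-III". There is also a general fallback: "nonparametric analysis will be used to analyse data that will not be normally distributed". The fallback test is not named, and nothing says whether it would be paired or unpaired.

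The article gives no number of blends, no number of tasters, no number of blends per taster and no expected spread or correlation of scores.

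**The concern.** People differ in how generously they use a nine-point scale. When one person scores several blends, that personal level is common to all of their scores and cancels out of a comparison between blends. A one-way ANOVA does not let it cancel. It leaves the taster variance in the error term, although the blend means no longer vary by that much relative to each other. The test then rejects less often than its nominal 5% when blends are equal, and has less power when they differ.

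What is at stake is modest but real. Sensory attributes are a declared outcome of work package 1 (Table 1 as acceptability, and Outcome measures variables), and taste helps to decide which bread is carried forward. A less sensitive test makes it harder to see that one candidate is liked less. The article fixes the test by name, so it is worth checking that the test suits the way the scores will be collected.

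**Working it through.** The plan gives no power, sample size or correlation for the sensory test, so there is no figure of its own to reproduce.

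**Inputs from the article.** One-way ANOVA; nine-point hedonic scores; alpha 0.05.

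**Assumed inputs.** Every taster scores every blend; k = 4 blends; n = 30 tasters (50 as a variant); total SD of a score 1; within-taster correlation rho from 0 to 0.5; one blend lower by 0.5 SD (0.75 SD as a variant).

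**Model.** Score = blend mean + taster effect (variance rho) + residual (variance 1 − rho).

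**Why the test is conservative.** With no blend difference, the between-blend mean square has expectation 1 − rho, because the taster effect cancels. The one-way error mean square, SSW / [k(n − 1)], has expectation 1. The true rejection rate is therefore about P(F > Fcrit / (1 − rho)) with k − 1 and k(n − 1) degrees of freedom. Here Fcrit(3, 116) = 2.683. At rho = 0.3 the effective threshold is 2.683 / 0.7 = 3.83, which gives 1.2%. At rho = 0.1 it is 2.683 / 0.9 = 2.98, which gives 3.4%.

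**Power of the blocked test.** The noncentrality is n × Σ(blend mean − grand mean)² / (1 − rho). One blend lower by 0.5 gives deviations of 0.125 (three times) and −0.375, so the sum of squares is 3 × 0.0156 + 0.1406 = 0.1875. At n = 30 and rho = 0.3 this gives 30 × 0.1875 / 0.7 = 8.04, and power from the noncentral F with 3 and 87 degrees of freedom is 63%.

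**Simulation** (40,000 runs per row, n = 30, one blend 0.5 SD lower):

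| rho | True size, one-way | Power, one-way | Power, blocked | Loss (points) |
|---|---|---|---|---|
| 0 | 5.2% | 48% | 47% | 0 |
| 0.1 | 3.6% | 46% | 52% | 6 |
| 0.2 | 2.2% | 44% | 57% | 13 |
| 0.3 | 1.2% | 42% | 64% | 22 |
| 0.5 | 0.2% | 37% | 80% | 43 |

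The simulated blocked powers agree with the noncentral F values to within a point.

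**Variants.**
- Gap of 0.75 SD, 30 tasters: one-way 85%, 87% and 88% against blocked 88%, 95% and 99% at rho 0.1, 0.3 and 0.5, a loss of 3, 9 and 11 points.
- Gap of 0.5 SD, 50 tasters: one-way 72%, 72% and 71% against 77%, 87% and 96%, a loss of 5, 15 and 25 points.
- Blend means evenly spaced over 0.5 SD, 30 tasters: 35% against 40%, 29% against 50% and 22% against 66%. Absolute power is lower and the loss about the same (5, 21 and 44 points). With this pattern, 50 tasters shrink the loss little: at rho 0.3 it is 54% against 75%.
- Scores rounded to nine points, 30 tasters: true size 3.4%, 1.3% and 0.2% at rho 0.1, 0.3 and 0.5, the same picture.

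**Other layouts.** If each taster scores one blend only, the independence assumption is met and the one-way test is correct. If separate panels score the same blend twice, the error runs the other way: with 4 blends, 10 tasters each, 2 scores per taster and rho 0.3, the true type I error is about 11%. The triplicate determinations in Statistical data analysis refer to nutrient measurements, so they are no evidence for that layout.

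**The case against.** The strongest objection is that no passage is shown to be wrong. Whether a taster scores several blends is not stated, and that is an operational detail which a journal article may leave to the full protocol. With separate tasters the named test is valid, and one sample per child avoids order, carry-over and fatigue effects. This stands, and it is why the point is conditional.

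Second, non-normal scores go to a nonparametric analysis, and nine-point scores may well take that route. This stands in part. The route does not settle the matter, because the test is unnamed: a Kruskal-Wallis test would ignore the pairing just as one-way ANOVA does, while a Friedman test would respect it.

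Third, a reader might infer that the test is far too conservative and that real differences will be missed. The documents do not support this. It needs a moderate or high correlation, which they do not give. At 0.1 the loss is about 6 points, and a gap of 0.75 SD is found with 85% power or more by the one-way test with 30 tasters.

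Fourth, a reader might infer that a less acceptable bread will go forward and that children will then eat less of it in the trial. No passage makes the choice of blend depend on a significant ANOVA. A lower-scoring blend would still show in the reported means, and the Discussion expects good acceptability and plans a further pre-test. The link to the amount eaten is speculation.

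**Conclusion.** The point holds in conditional form, as a cheap improvement and not as a demonstrated error. If tasters score more than one blend, the named test does not fit the data and is conservative. With 4 blends, 30 tasters and one blend 0.5 SD lower, the loss is about 6 points of power at correlation 0.1, 22 at 0.3 and 43 at 0.5, and the true size falls from 5% to about 3.6%, 1.2% and 0.2%. The number of blends, the panel size, the gap and the correlation are all assumptions, and so is the crossed layout itself. If each blend has its own tasters, one-way ANOVA is valid and nothing needs correcting. Either way the consequence stays within food selection in work package 1. The comparison of outcomes between the two schools in the pilot is not affected.

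**What to change.** 1. Under Acceptability, state who scores what. Preferably each taster scores every candidate blend, in randomised order, with a taster ID on the score sheet.
2. Under Statistical data analysis, replace one-way ANOVA of the hedonic scores by an analysis with taster as a block: two-way ANOVA, or a mixed model with blend fixed and taster random. Name the Friedman test as the nonparametric version. Report blend differences with 95% confidence intervals.
3. Keep one-way ANOVA only if each blend is scored by different tasters, and say so.

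The cost is about one line of analysis text and an ID field. The practical downside is that each child tastes a few samples in one session, which randomised order helps to balance but does not remove. Statistically almost nothing is lost: with zero correlation, power is 47% blocked against 48% one-way in the 30-taster example.
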